**Abstract**

| **（Keyword :** *COPD, Rhodiola L., clinical trial, biomarkers, spirometry, exercise testing, quality of life***）**  **BACKGROUNDS.** Chronic obstructive pulmonary disease (COPD) has been one of the top ten causes of death in our Taiwanese population. Most patients present dyspnea and exercise intolerance because of the deranged lungs and impaired skeletomuscular function. Recently, low-grade systemic inflammation plays a vital role in its pathogenesis. Despite the mainstay of treatment using the inhaled medications that may lead to slowdown the progression of impaired lung function, improve the quality of life, and reduce the episodes of acute exacerbation, in turn the systemic inflammation is on-going and is hardly controlled by local therapy.  Herb medicine like Rhodiola L extract capsule contains p-tryosol, salidroside, rosavin, pyridrde, rhodiosin and rhodionin and has its anti-inflammatory and anti-oxidative effects and minimum side-effect after a long-term use as reported in the literature.    **AIMS.** We hypothesize that add-on Rhodiola L extract capsule to the regimen of patients with moderate-to-severe COPD (1) may provide a potential of systemic effects of anti-inflammation and anti-oxidation for these patients, and these effects (2) may reflect in the improvement of patients’ physiological measurements, quality of life and exercise tolerance.  **METHODS**  [Study design] A randomized, double-blind, placebo-controlled clinical trial.  [Subjects] We will enroll 60 moderate-to-severe COPD patients aged 40-79 years, abstaining from cigarette smoking or maintaining a stable dose of cigarette consumption, no acute exacerbation of COPD, being stable for one month and longer, or not undergoing exercise training program. Patients should have no uncontrolled diabetes mellitus, uremia, chronic heart failure, cerebrovascular disease, uncontrolled anemia, late-stage malignant diseases, or other acute illness, or taking any systemic anti-inflammatory agents.  [Procedures and Randomisation] All elegible subjects with moderate-to-severe COPD will be enrolled after signing the informed consent. All subjects will undergo the first set of measurements as follows. All subjects will be allocated as the study designed. The study group will contain 40 subjects taking Rhodiola L extract capsule Rhodiola L 250 mg twice per day for 12 weeks and the control group will contain 20 subjects taking the placebo of the same dose for the same duration.  [Measurements Set] (1) demographics, (2) anthropometrics, (3) symptomatology: dyspnea index, cough, sputum, sleep, sex, (4) composite index: BODE, (5) quality of life, (6) lung function, 6MWT and exercise test, (7) COPD acute exacerbations, and (8) biomarkers: IL-1, TNF-, CRP, MMP-9, IL-4, and IFN-γ.  [Primary endpoint] Difference of 6 minutes walking distance at week 12. |

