| --- |

| **METHODS**  [Study design] A randomized, double-blind, placebo-controlled parallel clinical trial.  Randomization,  n=60  COPD  Study group, n=40  Week 0  Week 4  Week 8  Week 12  Control group, n=20  [Inclusion criteria] We will enroll 60 subjects with:   1. moderate-to-severe COPD patients 2. aged 40-79 years, 3. abstaining from cigarette smoking or maintaining a stable dose of cigarette consumption, 4. no acute exacerbation of COPD, 5. clinically being stable for one month and longer, 6. not undergoing exercise training program.   [Exclusion criteria] Patients should have no   1. uncontrolled diabetes mellitus by plasma fasting sugar >200 mg/dl, 2. uremia or CKD stage 5, 3. chronic heart failureby NYFC III, 4. cerebrovascular disease, 5. uncontrolled anemia by Hb < 10 mg/dl, 6. active malignant diseases, 7. other hospitalized acute illness, 8. systemic prednisolone > 10 mg per day.   [Randomisation] All legible subjects with moderate-to-severe COPD will be enrolled after signing the informed consent. All subjects will undergo the first set of measurements as follows. All subjects will be allocated in random order, double-blind, and placebo-control. The study group will contain 40 subjects taking Rhodiola L extract capsule Rhodiola L 250mg twice per day for 12 weeks and the control group will contain 20 subjects taking the placebo of the same dose for the same period of time. The placebo medication appears the identical figure and odor to the Rhodiola L extract capsule and is delivered by a pharmacist who is naïve to the measurement items and outcomes. The side effects and serious adverse effects of Rhodiola L extract capsule will be reported every time they occur by the patient and inquired monthly by the study nurse. Twelve weeks later, all subjects will undergo the second set of measurements. Each subject will revisit the out-patient clinic every month, totally four visits for each subject.  [Outcome measurements]  Primary endpoint: six-minute walk distance in meters at week 12.  Seconadary endpoins  (1) Demographics: age, body weight and height, gender measured by a study nurse  (2) Anthropometrics: mid-arm circumference and triceps skin thickness measured by a dietitian. See below.  (3) Symptomatology: dyspnea index: visual analog scale (VAS), exertional dyspnea: Borg scale12 and the modified Medical Research Council (mMRC)13, oxygen-cost diagram (OCD)14, cough: COPD assessment test (CAT) score, sputum: amount and color, evaluated by a study nurse  (4) Composite index: BODE15, the sum of B: BMI=body mass index, O: obstruction shown by FEV1%pred, D: dyspnea shown by themMRC.(5) Quality of life: Chronic respiratory disease questionnaire16 (CRDQ), St. George Respiratory disease questionnaire17 (SGRQ), hospital anxiety and depression scale18 (HADS), sleep quality: Epword Sleepiness scale, sex: International Index of Erectile Function (IIEF-5) evaluated by a study nurse.  (6) Lung function and 6-minute walk test (6MWT): spirometry, lung subdivisions, diffusing capacity for carbon monoxide, maximum inspiratory/expiratory pressure performed by a technician at the lung function lab of Da-Ching (大慶) Main Hospital. Protocol: see below. 6MWT19 will performed by the study nurse. Protocol: see below.  (7) Cardiopulmonary exercise test20 and 75% peak-work-rate constant work-rate exercise.21 All exercise tests will be performed by a technician at Zhong Xing (中興) Branch. Protocol: see below.  (8) Episodes of COPD acute exacerbations: recorded by a study nurse. Definition of acute exacerbation: more cough with more yellow sputum than usual or need more prednisolone for rescue or need antibiotics for possible infection or more dyspneic which makes the subject to visit the ER or to be hospitalized.  (9) Biomarkers: IL-1, TNF-, CRP, MMP-9.1, IL-4, and IFN-γ.  [Procedures]  *Anthropometric measurements.* Triceps skinfold thickness is measured with calipers, while the mid-upper arm circumference is measured with a tapeline. Both measurements are taken midway between the tip of the olecranon process and the acromion process, in the midline of the posterior surface of the extended dominant arm. All measurements are made thrice by an expericenced nutritionist and the middle value is recorded for analysis.  *Lung function test protocol.* Pulmonary function tests are performed before exercise testing to identify moderate-to-severe COPD. FEV1 is measured with a mass flow sensor spirometer (Yorba Linda, CA, USA) at body temperature, ambient atmospheric pressure, and fully saturated (BTPS). The best of three technically satisfactory readings is used. The total lung capacity (TLC), residual volume (RV), and carbon monoxide diffusing capacity (DLCO) are also measured (Yorba Linda, CA, USA). All the lung function data are obtained after inhaling 400 g of fenoterol HCl. DLCO is measured by the single-breath technique. Simple volume calibration is conducted with a 3-L syringe before each test. For the predicted race-adjusted values of FEV1, forced vital capacity (FVC), TLC, and DLCO used by the institution, please refer to selected reference.[19,22-24](#_ENREF_13) Maximum inspiratory pressure (MIP) at the mouth is measured at RV with a forceful inspiratory maneuver leading to a sustained maximal effort followed by natural release upon fatigue (Yorba Linda, CA, USA). Maximum expiratory pressure (MEP) is measured at TLC. MIP and MEP are both performed on three occasions with a 1-minute recovery period between efforts. The best result is recorded for analysis. For determining breathing reserve, the direct maximum voluntary ventilation (MVV) is calculated from a 12-second maneuver of rapid and deep breathing as recommended for COPD patients [25](#_ENREF_17).  *Six-minute walk test protocol*. The walk tests are conducted in a temperature-controlled corridor. Before and immediately after the walk test, systemic arterial blood pressure and respiratory frequency are measured. The perceived exertion is measured with a modified Borg score at rest, midway through and at the end of the walk. Patients are instructed to walk as far as possible with the help of verbal encouragement by an experienced investigator, as Guyatt et al.26 recom-mended. Patients are allowed to stop to rest if needed. Oxyhaemoglobin saturation determined by pulse oximetry (SPO2) (Ohmeda 3760) and the heart rate readings are stored and later printed out as 15-sec averages. The absolute change in the heart rate in response to walk test is the difference between the baseline and the end. The change in SPO2 is the absolute change from the baseline to the nadir during the walk. Each patient performs two to three repetitions of walk tests separated by 2±4 h of rest. The highest distance walked in the 6 min (D) is recorded in meters. The distance is then converted to DW by multiplying by the body weight in kilograms.19  *Cardiopulmonary exercise test protocol.* After acclimating to the computer-controlled and electronic-braked cycle ergometer (Yorba Linda, CA, USA) and a 2-minute rest period, each patient began a 2-minute period of unloaded cycling followed by a ramp-pattern exercise test to the limit of their tolerance. Work rate is selected at a slope of 5 to 20 watts per minute according to pre-determined fitness based on our derived protocol formula.[14](#_ENREF_18)  Twelve-lead electrocardiography, heart rate, oxyhemoglobin saturation (SPO2), O2 (ml/min), CO2 (ml/min), minute ventilation (E), blood pressure, and Borg score were measured. Heart rate and SpO2 using a pulse oximeter (Ohmeda 3740, BOC Health Care Company, CO, U.S.A.) were measured continuously. Borg score was used to rate the perceived dyspnea from a scale of 0 to 10 during the course of exercise testing following appropriate instruction before exercise testing.[12](#_ENREF_19) Calibrations of the preVentTM pneumotachograph were performed with a 3-L syringe before each test. The O2 and CO2 analysers were calibrated with standard gases. The anaerobic threshold was determined using dual method approach [20](#_ENREF_1) containing modified V-slope method [27](#_ENREF_20) and the ventilatory equivalents methods. [28](#_ENREF_9)  The study will cover the expenditure of hospitalization that the adverse events related, although the advert events should be extremely low. The study will offer a 24-h a day service if the participants have any adverse events to report. All the study materials will be preserved safely at our study site.  **Biochemical diagnosis**  Measurement of routine blood indices, including alanine transaminase (ALT), aspartate aminotransferase (AST), creatinine, and blood urea nitrogen (BUN) detection (Automatic analyzer, ARCO, Biotechnica Instruments, Italy) will be processed at the indicated time.  **Cytokine determination**  Cytokine determination by ELISA according to the manufacturer’s instructions (Pharmingen, San Diego, CA, USA). Cytokines (IL-1, TNF-, CRP, MMP-9, IL-4, and IFN-γ) were assayed in triplicate using commercial ELISA kits as described elsewhere (Tsai et al., 2000; Lin et al., 2004; Ho et al., 2005; Huang et al., 2005; Lin et al, 2005a, 2005b, Lin et al., 2006). Using 96-well plates, 100 μl anti-mouse capture antibody diluted 1:250 was added and incubated overnight at 25°C. Serum samples or the standard were added (100 l/well), and plates were incubated at 25°C for 2 h. After incubation, plates were washed five times with ELISA washing solution, and 100 μl biotinylated anti-mouse monoclonal antibody conjugated to horseradish peroxidase, diluted 1:250 in assay diluents, was added to each well. Plates were incubated at room temperature for 1 h. After incubation, the wells were washed seven additional times with ELISA washing solution using an ELISA washer (Bio-Rad, Hercules, CA, USA). Substrate solution (tetramethylbenzidine, 100 l) was added, and the plates were incubated at 37°C for 15 min. The reaction was then terminated by the stop solution (2N H2SO4), and absorbance was read at 450 nm with a spectrophotometer (Model 550, Bio-Rad). For every test, a standard curve was also derived for IL-4 and IFN-γ. The range of the standard curve extended from and 15.6 pg–8000 pg for IFN-γ.  試驗品部分(劑量與用法)：  試驗物質類別型態： 紅景天濃縮細粒  衛署藥製第055161號  主要成分：   | 處方成分 | | | | --- | --- | --- | | 成分內容 | 成分數量 | 成分單位 | | 紅景天 | 1.5 | g | | 以上生藥製成浸膏0.45g(生藥與浸膏比例1.5：0.45＝3.3：1) |  |  | | 微結晶纖維素 | 0.35 | g | | starch | 0.2 | g |   包裝方式：4~1000公克塑膠瓶裝  規格與濃度：500mg/顆  儲存溫度：室溫陰涼通風處  用量用法：紅景天組:成人每日1次、每次1顆 (與食物錯開至少半小時，配溫開水服用)    Statistical analysis：  The intent-to-treat analysis was used in the study. Data were summarized as mean  standard deviation (SD) or median (interquartile). A linear mixed model was used to compare the means in each variable between pre- and post- interventions and to test these pre-post differences between the study and the placebo groups. For each variable, the comparisons were planned priori and were simultaneously performed by setting up appropriate dummy variables and interactions with random effects in linear mixed models. For non-normal data, the Mann-Whitney test was used. The chi-square test or Fisher exact test was used to compare the proportion of the categorical variables between the two groups. A *p* value of less than .05 was considered to be statistically significant, and a *p* value of less than .1 but more than .05 was considered to have a trend. Statistical procedures were performed using the SAS software package version 9.3 (SAS Institute Inc., Cary, NC) and Microcal Origin v 4.0 (Northampton, MA, USA).  We estimated that there was a statistical power of 0.8 for 6MWD, given the 6MWD in the study from 456 meters to 482 meters in the study group and no improvement in the control group, the sample size is 60 subjects including an expected 20% dropout rate.   |  | | | | | | | --- | --- | --- | --- | --- | --- | | week  variables | week 0 | week 4 | week 8 | week 12 | note | | (1)physical examination |  |  |  |  |  | | (2)CRDQ |  |  |  |  |  | | (3)SGRQ |  |  |  |  |  | | (4)HADS |  |  |  |  |  | | (5)BDI |  |  |  |  |  | | (6)TDI |  |  |  |  |  | | (7) adverse effects |  |  |  |  |  | | (8)CRE |  |  |  |  |  | | (9)CBC |  |  |  |  |  | | (10)GPT |  |  |  |  |  | | (11)lung function |  |  |  |  |  | | (12)cardiopulmonary exercise test |  |  |  |  |  | | (13)6MWT |  |  |  |  |  | | (14) IL-1 |  |  |  |  |  | | (15)TNFα |  |  |  |  |  | | (16)HS-CRP |  |  |  |  |  | | (17)MMP9 |  |  |  |  |  | |

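### No primary comparison is named for 6MWD, and the planned between-arm test of changes, though valid, leaves unused the precision of a baseline already measured

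*Protocol*

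**What the plan says.** All of this is in the protocol; no SAP was available.

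- **Endpoint.** METHODS, Outcome measurements: "Primary endpoint: six-minute walk distance in meters at week 12". The Abstract: "Difference of 6 minutes walking distance at week 12", without saying whether the difference is between arms or from baseline.
- **Model.** METHODS, Statistical analysis: "A linear mixed model was used to compare the means in each variable between pre- and post- interventions". That sentence then adds a second use of the model, a comparison of those changes across the two arms. On how the tests are carried out, the protocol states: "the comparisons were planned priori and were simultaneously performed by setting up appropriate dummy variables and interactions with random effects". No baseline covariate is named, and nothing is said about constraining the baseline means.
- **Fallback.** "For non-normal data, the Mann-Whitney test was used"; whether it is applied to the week-12 value or the change is not stated.
- **Threshold.** "value of less than .05 was considered to be statistically significant", with values between .05 and .1 labelled a trend. The text does not say whether the test is one- or two-sided.
- **Power.** "We estimated that there was a statistical power of 0.8 for 6MWD", based on a rise from 456 to 482 m in the study group and none in control, with 60 subjects (40 and 20) including 20% dropout. No SD or correlation is given.

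**The concern.** Two kinds of comparison sit side by side at the same threshold: a pre-post comparison and a between-arm comparison of the pre-post changes. Only the second bears on the drug effect, yet the text does not single it out.

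The between-arm contrast also appears to leave precision unused. METHODS describes two sets of measurements, at entry and after twelve weeks. With two time points and complete data, a model with group, time and their interaction, and baseline means left free, gives exactly the difference between arms in mean change. Baseline 6MWD then enters with a fixed weight of one rather than the weight the data support.

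What is at stake is some precision in a trial expecting 48 completers, and clarity about which p-value carries the primary result. The second matters because 6MWD is an effort-dependent test done with encouragement, so improvement in both arms is possible. The active arm is twice the size, so an equal gain reaches within-arm significance more easily there.

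**Working it through.** **Inputs from the protocol.** Effect 482 − 456 = 26 m. Completers 60 × 0.8 = 48, split 2:1 as 32 and 16. Alpha 0.05, taken as two-sided. **Assumed:** SD, correlation r, and any gain shared by both arms.

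**1. The stated sample size.** N = 60 cannot be reproduced because no SD is given. Solving backwards by the normal approximation: SD = 26 / [(1.960 + 0.842) × √(1/32 + 1/16)] = 26 / (2.802 × 0.306) ≈ 30.3 m. The stated size fits a between-arm comparison only if the analysed quantity has an SD of about 30 m.

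**2. Precision.** With equal SD s at both times, the per-patient variances are:
- change: 2s²(1 − r)
- baseline-adjusted: s²(1 − r²)
- ratio of adjusted to change: (1 − r²) / [2(1 − r)] = (1 + r)/2

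The ratio is below 1 for every r below 1, apart from the one residual degree of freedom spent on the covariate. Extra completers are 48/ratio − 48. Power below uses the t-test with s = 80 m (assumed), 26 m and 32/16.

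| r | Variance saved | Worth in completers | SD of change | Adjusted SD | Power, change | Power, adjusted |
|---|---|---|---|---|---|---|
| 0.5 | 25% | 16 | 80.0 | 69.3 | 18% | 22% |
| 0.6 | 20% | 12 | 71.6 | 64.0 | 21% | 25% |
| 0.8 | 10% | 5 | 50.6 | 48.0 | 38% | 41% |
| 0.9 | 5% | 2–3 | 35.8 | 34.9 | 64% | 66% |

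The gain is about 2 to 4 points. If instead the SD of change is held at the back-solved 30.3 m (normal approximation), power rises from 80% to 90% at r = 0.5, 84% at 0.8 and 82% at 0.9.

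**3. Within-arm p-values with no drug effect.** Suppose both arms gain m metres. Each arm's paired t-test has noncentrality m/(SD/√n), with n = 32 or 16. The arms are independent, so P(active significant, placebo not) = P₃₂ × (1 − P₁₆). For SD 40 m and m = 15 m: 0.538 × (1 − 0.290) = 0.38.

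| Shared gain | Change SD 40 m | Change SD 50 m |
|---|---|---|
| 0 m | 5% | 5% |
| 5 m | 10% | 8% |
| 10 m | 24% | 17% |
| 15 m | 38% | 30% |
| 20 m | 42% | 40% |
| 26 m | 30% | 41% |

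The zero row is 0.05 × 0.95 = 4.75%; half of it is improvement and half deterioration. The between-arm test stays at 5% in every row, because the shared gain cancels.

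**The case against.** **A valid test is already there.** The between-arm comparison of changes is unbiased under randomisation and holds its 5% level. Preferring an adjusted analysis is a matter of efficiency, not the repair of an error. This stands.

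**The model may already be adjusted.** The text mentions only dummy variables, interactions and random effects, and a mixed model with baseline means constrained equal would fit those words. Covariates are often left to the SAP. This stands in part: the unadjusted contrast is the natural reading, not a certain one. The lack of a covariate is therefore not an omission; the point is that a better choice is free.

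**Three competing primary analyses?** A reader might infer that a raw week-12 comparison, a within-arm test and a change contrast all coexist as primary readings. The documents do not support that. The endpoint sentence names a variable and a time point, not a test. The power sentence sets a gain in one arm against none in the other, which agrees with the model's between-arm contrast. The model sentence plans no raw week-12 test, so the 18% power of such a test (SD 80 m) does not describe the plan. Only the Mann-Whitney fallback, with its outcome unstated, leaves that open.

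**A built-in route to a false claim?** A reader might also infer that significance on drug but not on placebo would count as success. Nothing says so. The pre-post clause does not even specify that the test is within each arm, and comparing the changes between arms is the safeguard against that fallacy. The 30–42% figures need a shared gain of 15–26 m that the protocol does not document; it assumes no improvement in control. Repeating the walk two to three times per session and keeping the best may also limit practice gains.

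**Conclusion.** The point holds as a worthwhile, cost-free improvement. The plan contains a valid between-arm test but does not name it as the primary one, and it sets pre-post comparisons beside it at the same threshold.

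The precision argument is certain in direction and modest in size: the ratio (1+r)/2 is algebra under equal SDs, but r and the SD are assumptions. The risk from within-arm p-values is conditional: about the nominal 5% with no shared gain, and substantial only if both arms improve by roughly 10 m or more at the assumed change SDs. It concerns how results could be read, not a decision rule in the protocol. The missing SD behind N = 60 is a separate matter that baseline adjustment does not cure.

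**What to change.** - Name one primary test: the between-arm difference in 6MWD at week 12 with baseline 6MWD as covariate, or the planned mixed model with the two baseline means constrained equal. Use two-sided 0.05 and report the estimate with its 95% CI.
- Word the endpoint identically in the Abstract and in Outcome measurements, as that between-arm difference.
- Report within-arm pre-post changes descriptively, without p-values.
- Use the same model for the continuous secondary endpoints.

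The cost is a few sentences of analysis text. Baseline 6MWD is already measured, so no patients, visits or data are added, and the constrained version stays within the planned model family.

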| study nurse | [name] | screening, assist to conduct the study |
| study nurse | [name] | screening, assist to conduct the study |

| series no. | specification | no | price | unit | total (NT) |
| --- | --- | --- | --- | --- | --- |
| 1 | Microcentifuge tubes, pipets, pipet tips, kimwipe, gloves,test tube | 8 | 6,000 | 盒 | 48,000 |
| 2 | Import RT (A3800) kit | 2 | 17,200 | kit | 34,400 |
| 3 | RQ1 RNase-free DNase | 1 | 3,000 | vial | 3,000 |
| 4 | ImProm-II Reverse transcriptase | 2 | 8,000 | vial | 16,000 |
| 5 | goTaq qPCR master mix | 2 | 10,000 | ea | 20,000 |
| 6 | Primer | 364 | 32 | mer | 11,648 |
| 7 | RNA spin minikit | 2 | 8,500 | kit | 17,000 |
| 8 | PCR tube | 3 | 7,000 | box | 21,000 |
| 9 | PCR strip | 3 | 7,500 | box | 22,500 |
| 10 | IL-2 ELISA kit | 2 | 17,500 | kit | 35,000 |
| 11 | IL-4 ELISA kit | 2 | 17,500 | kit | 35,000 |
| 12 | IL-10 ELISA kit | 2 | 17,500 | kit | 35,000 |
| 13 | IFN-g ELISA kit | 1 | 17,500 | kit | 17,500 |
| 14 | BUN Biochemistry analyses | 1 | 11,000 | kit | 11,000 |
| 15 | Creatinine Biochemistry analyses | 1 | 11,000 | kit | 11,000 |
| 16 | ALT Biochemistry analyses | 1 | 11,000 | kit | 11,000 |
| 17 | AST Biochemistry analyses | 1 | 11,000 | kit | 11,000 |

| no | item | use | multiple | price | unit | total (NT) |
| --- | --- | --- | --- | --- | --- | --- |
| 1 | IRB | review fee | 1 | 5000 | time | 5,000 |
| 2 | pharmacy administration fee | study drug and placebo | 1 | 60000 | year | 60,000 |
